### Analyses and statistical methods

Using an intention-to-treat approach, the primary study analysis will use a baseline covariate-adjusted time-to-event individual patient-level analysis (proportional hazards model, if appropriate) to estimate the relative effectiveness of the two prescribing policies in preventing the primary outcome. We will adjust for a range of pre-specified covariates, including age, sex, co-morbidities and the Scottish Index of Multiple Deprivation [35]. This primary analysis will be of most use to policymakers in determining whether, as NICE guidance suggests, prescribers should be directed to favour one drug over the other.

We will perform a similar analysis using an as-treated approach to estimate the relative effectiveness of the two medications in preventing the primary outcome. This analysis will address the cited lack of direct comparative effectiveness evidence for these two drugs.

Randomisation and the large sample size (i.e. a large number of practices randomised) should reduce bias from an imbalance of baseline covariates. However, a range of sensitivity analyses will be performed to explore residual biases, including selection bias and differential adherence.

A detailed statistical analysis plan will be prepared and published.

#### Sample size

EVIDENCE is a cluster randomised study; statistical power, therefore, depends on the number of practices, the mean number of patients in each practice and the event rate and their variability between practices. We used data obtained from the Clinical Practice Research Datalink for the Bendroflumethiazide versus Indapamide for Primary Hypertension: Observational (BISON) study to estimate these variables [36]. First, we identified patients similar to the expected EVIDENCE study population and found an average of 200 individuals per practice, but with substantial variation in numbers between practices (standard deviation 140). We then defined an arbitrary index date and calculated the incidence of the EVIDENCE composite endpoint following that date. The overall event rate was 0.0305 per patient-year (0.0265 in patients with no previous outcome event and about six times higher in the 7% of follow-up time for patients with an earlier event). Finally, we estimated the between-practice standard deviation to be 0.0047.

Using these parameters, we ran simulations using random samples of 250 practices (sample size 50,000) with a mean follow-up time of 2 years and clinically plausible relative risks between treatments of 1.1 to 1.2. We also allowed the possibility that the BISON study overestimated the event rate by a factor of 2 or 3. We fitted mixed-effects models, in which variation between practices was treated as a random effect, and prior history was treated as a patient-level fixed effect, to estimate the confidence interval for the relative risk between treatments. Finally, we conducted a 2-sided test of the superiority of one treatment over the other. Assuming event rates are close to those found in the BISON study, a study size of 50,000 individuals (250 practices) will have 80% power to detect a relative risk of about 1.12 between treatments. If the event rate is 2 or 3 times lower, this study will have 80% power to detect relative risks of 1.16 and 1.19, respectively.

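### The four event-rate figures in the sample size section do not reconcile: the two subgroup rates imply 0.0358 per patient-year overall, not the stated 0.0305

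*Protocol article*

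**What the plan says.** All the relevant figures stand in the Sample size section of the protocol article and come from the observational planning dataset.

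- Overall rate: "The overall event rate was 0.0305 per patient-year".
- The split, in the bracket that follows directly: "0.0265 in patients with no previous outcome event and about six times higher in the 7% of follow-up time", the 7% being the time of patients with an earlier event.
- Variation of the rate between practices: "we estimated the between-practice standard deviation to be 0.0047".
- Practice size: "an average of 200 individuals per practice, but with substantial variation in numbers between practices (standard deviation 140".
- Design simulated: "random samples of 250 practices (sample size 50,000) with a mean follow-up time of 2 years".

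The next paragraph opens with "Using these parameters, we ran simulations", which makes these figures the inputs to the power calculation. The simulated mixed model includes prior history as a fixed effect for each patient, so the subgroup rates matter as well as the overall rate. The section reports 80% power for a relative risk (RR) of about 1.12 at the planning rate, and for 1.16 and 1.19 if the rate is two or three times lower. No other section gives an event rate.

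**The concern.** An overall rate per patient-year is the average of the subgroup rates, weighted by each subgroup's share of follow-up time. The article gives the overall rate, one subgroup rate, the ratio between the subgroups and the time share. Any three of these fix the fourth. The printed four do not agree, and the gap is too wide for rounding.

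All three power statements rest on these inputs. As printed, a reader cannot tell whether the simulation used the overall figure or the subgroup figures, and so cannot reproduce it. The protocol also allows for the planning rate being two or three times too high, and that scaling needs an unambiguous starting value.

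**Working it through.** **Inputs** (all from Sample size): overall rate 0.0305; rate without an earlier event 0.0265; ratio about 6; share of follow-up time with an earlier event 7%, hence 93% without; 250 practices, mean size 200, SD 140; mean follow-up 2 years; between-practice SD 0.0047.

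**Step 1. Try to reproduce 0.0305.** Overall = 0.93 x 0.0265 + 0.07 x 6 x 0.0265 = 0.024645 + 0.01113 = 0.035775. This is 0.035775 / 0.0305 = 1.17 times the stated value, which is not reproduced.

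**Step 2. Rounding and wording.** Write overall = base x (1 + share x (ratio - 1)).

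- Lowest with rounding: 0.02645 x (1 + 0.065 x 4.5) = 0.0342.
- Highest with rounding: 0.02655 x (1 + 0.075 x 5.5) = 0.0375.
- Ratio stretched down to 5, other inputs at their lowest: 0.02645 x (1 + 0.065 x 4) = 0.0333.
- Six times higher read as sevenfold: 0.0376.
- Six times the overall rate: 0.93 x 0.0265 + 0.07 x 6 x 0.0305 = 0.0375.

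No reading reaches 0.0305.

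**Step 3. What would have to change to keep 0.0305.**

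- Ratio: (0.0305 / 0.0265 - 0.93) / 0.07 = 3.2 (3.0 to 3.4 with rounding).
- Time share: (0.0305 / 0.0265 - 1) / 5 = 3.0%.
- Base rate: 0.0305 / 1.35 = 0.0226.

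None of these is a rounding of the printed figure.

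**Step 4. Expected events.** 50,000 x 2 = 100,000 patient-years. This gives 3,050 events at 0.0305 and about 3,580 at 0.0358, a gap of about 530.

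**Step 5. Effect on the detectable RR.** The article gives no alpha; two-sided 0.05 is assumed. For practice i of size m_i, expected events are e_i = m_i x 2 x rate. Information = sum over practices of 1 / (1/e_i + CV^2), with CV = 0.0047 / 0.0305 = 0.154. SE of log RR = 2 / sqrt(information). Detectable RR at 80% power = exp(SE x (1.960 + 0.842)).

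Example at 0.0305 with equal practices: e = 200 x 2 x 0.0305 = 12.2. Information = 250 / (1/12.2 + 0.154^2), about 2,365. SE is about 0.0411 and detectable RR is 1.122.

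With gamma-distributed practice sizes (SD 140; the shape is assumed) and CV held at 0.154:

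| Event rate | Stated RR | From 0.0305 | From 0.0358 |
|---|---|---|---|
| Full | 1.12 | 1.127 | 1.120 |
| Half | 1.16 | 1.171 | 1.159 |
| One third | 1.19 | 1.206 | 1.191 |

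With equal practice sizes the columns become 1.122, 1.166, 1.202 and 1.115, 1.154, 1.187. If the SD of 0.0047, not the CV, is held fixed at the rate of 0.0358, unequal sizes give 1.114, 1.154, 1.187.

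Power at RR 1.12 is 0.755 from 0.0305 (0.787 with equal sizes) and 0.802 from 0.0358 (0.833 with equal sizes).

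**The case against.** The strongest reply is that the averaging identity holds only if all four figures share one base. One of them may count first events only, or the ratio may be defined in a way the article does not spell out. That stands: the discrepancy shows that a figure is wrong or is on an unstated base, and not which of the two. A reader might infer that 0.0358 is the true overall rate. The article does not support that; 0.0358 is only what the printed subgroup figures imply.

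A second reply is that the design hardly depends on the answer. This largely stands too. The detectable RR at the full rate moves by about 0.007 with CV held, every value obtained is near 1.12, and the protocol already considers rates two or three times lower, a far wider range than 17%. A reader might infer that the trial is underpowered or that its simulation was wrong. Neither follows, because the stated RRs fit the subgroup rates well and the error may lie only in the summary figure.

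A reader might also infer that the uncertain event count undermines the running of the trial. Nothing in the article supports this. The target is set in practices, patients and follow-up time, no event target is given, and the monitoring committee is to judge relative risk and benefit.

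What the replies do not remove is the contradiction itself. The article prints all four numbers, so this is not detail left to a fuller document.

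**Conclusion.** The point holds as an inconsistency among stated planning inputs. The subgroup figures imply 0.0358 per patient-year, 17% above the stated 0.0305, and neither rounding nor any alternative reading of the sixfold ratio closes the gap. Which figure is at fault cannot be settled from the article.

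The consequence is modest. The stated 1.12, 1.16 and 1.19 fit the subgroup rates better than 0.0305 once variation in practice size is included. This suggests, but does not prove, that the simulation used the subgroup rates. If 0.0305 is the true rate, power at RR 1.12 is about 76%, or 79% with equal practice sizes, slightly short of the stated 80%.

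The rate arithmetic needs no assumption beyond a common base for the four figures. The power figures are approximate: they assume two-sided alpha 0.05 and gamma practice sizes, read 0.0047 as true between-practice variation, and leave out the prior-history term of the simulated model.

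**What to change.** Go back to the planning dataset and check the overall rate, the rate without an earlier event, the ratio and the time share. Correct whichever is wrong. If none is wrong, state the base of each, in particular whether any counts first events only. Say which rates entered the simulation, and give the expected number of events.

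If the simulation inputs prove wrong, re-run it and restate the three detectable RRs. If they were right and only the summary figure is off, correct that figure and leave the power statements as they are. The cost is one corrected paragraph and, only in the first case, a simulation re-run. Nothing in the conduct of the trial changes.

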### Cluster randomisation

The randomisation unit in this study is the practice (the cluster); patients are not individually recruited. Following identification and approval of the practice study population, the practice will be randomised using an online study portal. Randomisation will be 1:1, block balanced by practice list size, using a computerised randomisation algorithm. Block sizes are randomly allocated to prevent staff implementing the trial from guessing the next allocation. The prescribing policies will be applied at a practice level, and individual prescribers will remain free to prescribe as clinically appropriate.

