### Policy implementation

#### Informing patients about the study

Immediately following randomisation of a practice, all patients in the study population will be written to informing them that their practice is taking part in the EVIDENCE study. The letter will be printed on practice-specific headed paper and will briefly explain why the study is being conducted. It will also advise that the patient's repeat prescriptions for thiazide-type medication may be switched in line with the newly assigned practice prescribing policy. The letter directs patients who may have any questions, concerns, or objections to visit a study-specific website (www.memoresearch.com/evidence) or directly contact the study team. The study team will provide further information and, if the patient confirms that they would prefer to opt-out of any switch and remain on their current medication, the study team will not action the switch for that individual.

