## Discussion

EVIDENCE uses a new pragmatic trial method, combining essential elements of randomised clinical trials and observational analysis of routine clinical data collection and making use of routine NHS prescribing management activities. Cluster randomisation allows very large numbers of patients to be rapidly included in a study, facilitating an adequately powered study of short duration. This method provides a research infrastructure for rapid and highly efficient generation of evidence of comparative effectiveness of medications in situations where clinical equipoise exists.

In addition to the sample size considerations described above, cluster randomised trials are potentially vulnerable to significant imbalance in baseline covariates, leading to reduced statistical precision [24]. Although we have used block randomisation stratified by practice size to mitigate some cluster-level covariate imbalance, this may not be sufficient to account entirely for imbalance in cluster and individual patient-level baseline covariates, despite the relatively large number of clusters. For this reason, we plan a covariate-adjusted statistical analysis. Alternative methods of achieving balance at baseline, such as minimisation or covariate-constrained randomisation, should be considered for future trials using this design [24]. However, such approaches may be limited by lack of access to suitable data to calculate baseline covariate means and would increase the complexity of the study implementation in individual practices.

The primary intention-to-treat analysis will be susceptible to bias due to differential adherence. Although patients will not pay for either medication (all prescriptions are free within the NHS in Scotland), we may still expect differences in medication adherence between arms. For example, a patient experiencing minor symptoms may be more likely to attribute them to a new-to-them medication and discontinue or take the medication only intermittently, compared to a similar patient whose prescription has been unchanged. Therefore, the planned secondary as-treated analysis using dispensed prescribing data will be essential to interpreting the results.

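### The relative risks of 1.12, 1.16 and 1.19 quoted as detectable between treatments are ratios between policies; power against a drug ratio of the same size is lower

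*Protocol article*

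**What the plan says.** The Sample size section of the protocol article bases its simulations on "random samples of 250 practices (sample size 50,000) with a mean follow-up time of 2 years". The effects put into them are described as "clinically plausible relative risks between treatments of 1.1 to 1.2". The other inputs are practice size (mean 200, SD 140), the event rate, the between-practice SD of that rate (0.0047) and prior history of an event. Mixed-effects models were fitted and, in the authors' words, "we conducted a 2-sided test of the superiority of one treatment over the other". The conclusion is that the study "will have 80% power to detect a relative risk of about 1.12 between treatments"; at half or one third of the event rate, "this study will have 80% power to detect relative risks of 1.16 and 1.19, respectively".

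The section on analyses and statistical methods keeps two questions apart. The primary intention-to-treat analysis estimates the relative effectiveness of the two policies. A separate as-treated analysis addresses the two medications.

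The study population is the list that the practice approves before it is randomised (Exclusion criteria; Cluster randomisation). Patients are told of the study after randomisation. If one declines, "the study team will not action the switch for that individual". Under the policy, "individual prescribers will remain free to prescribe as clinically appropriate". The Discussion adds: "The primary intention-to-treat analysis will be susceptible to bias due to differential adherence".

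**The concern.** A ratio between drugs and a ratio between policies are equal only if every patient in each arm takes that arm's drug. Here the design allows otherwise. A patient who opts out of the switch, is switched back or is prescribed off policy takes the other arm's drug but is still analysed in the arm of the practice. Each such patient narrows the difference between the arms in what is actually taken, and with it the effect that the primary test can see.

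The article judges its power against a range of plausible ratios of 1.1 to 1.2 described as lying between treatments. If the stated 80% belongs to the policy ratio, a reader who takes 1.12 as the detectable difference between indapamide and bendroflumethiazide credits the primary analysis with more power than it has for that difference.

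**Working it through.** **Step 1: reproduce the stated figures with full contrast.** Inputs from Sample size: 250 practices (125 per arm under 1:1 allocation), mean size 200, SD 140, 2 years' mean follow-up, rate 0.0305 per patient-year, between-practice SD 0.0047. The two-sided alpha is not stated; 0.05 is assumed.

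- Events: 50,000 × 2 × 0.0305 = 3,050.
- Between-practice coefficient of variation: 0.0047 / 0.0305 = 0.154; squared, 0.0237.
- Ignoring clustering: detectable RR = exp(2.80 × 2 / √3,050) = 1.107.
- Design effect, equal practice sizes: 1 + 200 × 2 × 0.0305 × 0.0237 = 1.29; detectable RR 1.122.
- Design effect, unequal sizes: the size-weighted mean is 200 × (1 + 0.7²) = 298, so 1 + 298 × 2 × 0.0305 × 0.0237 = 1.43; detectable RR 1.129. Weighting each practice by the inverse of 1/(size × 2 × rate) + CV² gives 1.127.

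The component rates in the same section imply a higher overall rate: 0.0265 × (0.93 + 0.07 × 6) = 0.0358. That mismatch with 0.0305 is a separate matter. With 0.0358, unequal sizes, inverse-variance weights and CV 0.154:

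| Event rate | Stated RR | Recomputed RR | Power at stated RR |
|---|---|---|---|
| as found | 1.12 | 1.120 | 80.1% |
| half | 1.16 | 1.159 | 80.5% |
| one third | 1.19 | 1.191 | 79.5% |

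All three figures are recovered with no loss of contrast. At 0.0305 with unequal sizes the detectable ratio is already slightly worse than stated. On neither rate is there a sign of a hidden allowance for non-uptake.

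**Step 2: translate to the drug scale.** Let d be the share of the between-arm contrast in drug taken that is lost because patients take the other arm's drug, added over both arms. Then

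- ln RR(policy) = (1 − d) × ln RR(drug);
- power at a drug RR equal to the stated value = Φ(2.80 × (1 − d) − 1.96), holding the precision implied by the stated 80%;
- drug RR detectable with 80% power = exp(ln RR(stated) / (1 − d)).

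Example, d = 10%: 2.80 × 0.90 − 1.96 = 0.56, and Φ(0.56) = 71%. Also ln 1.12 = 0.1133; 0.1133 / 0.90 = 0.1259; exp(0.1259) = 1.134.

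| d (assumed) | Power at drug RR 1.12 | Drug RR for stated 1.12 | for 1.16 | for 1.19 |
|---|---|---|---|---|
| 0 | 80% | 1.120 | 1.160 | 1.190 |
| 5% | 76% | 1.127 | 1.169 | 1.201 |
| 10% | 71% | 1.134 | 1.179 | 1.213 |
| 20% | 61% | 1.152 | 1.204 | 1.243 |
| 30% | 50% | 1.176 | 1.236 | 1.282 |

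**Step 3: check the form of the dilution.** An additive mixture in one arm, 1 + 0.12 / (1 − d), gives 1.126, 1.133, 1.150 and 1.171 for the 1.12 column, so the log-linear form matters little.

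**The case against.** The strongest reply is that nothing is miscalculated. The trial tests policies, its power should be given on the intention-to-treat scale, and treatments can be read as the randomised arms. On that reading 1.12 stands. This is right as far as it goes, and a reader who inferred a wrong sample size calculation would go too far. But the analysis section distinguishes policies from medications, and the Sample size section then uses a word that does not say which is meant.

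Full uptake is also inferred rather than stated. Simulating a policy ratio of 1.12 and simulating a drug ratio of 1.12 with complete uptake give the same numbers, so Step 1 cannot tell them apart. It does not need to: under either, the figure is detectable on the policy scale only.

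The size of d is unknown, and the design limits it. Unsuitable patients are removed before randomisation, patients already on the policy drug are not switched, and because bendroflumethiazide is the dominant drug, opting out matters mainly in the indapamide arm. At 5% to 10% the change from about 1.12 is small. Even at 30% the first figure, 1.176, stays inside the range of 1.1 to 1.2.

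Two stronger readings are tempting and unsupported. The first is that all non-adherence pulls the result towards 1 and so favours a finding of no difference. That holds for taking the other arm's drug, but not for stopping treatment altogether. With assumed values, if the drugs are equal, 10% of one arm stop, and untreated risk is 1.3 times higher, the policy ratio is 0.90 + 0.10 × 1.3 = 1.03, away from 1. The Discussion's own example concerns discontinuation or intermittent use after a switch, and it speaks of bias, not dilution. The second is that a stated equivalence power is overstated. The title calls this an equivalence trial, but the Sample size section reports a superiority test and no equivalence power.

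Finally, the article acknowledges differential adherence and plans as-treated and sensitivity analyses. These address the drug question but do not restore the power of the primary test.

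**Conclusion.** The point holds as one of labelling and missing translation. The ratios 1.12, 1.16 and 1.19 are detectable ratios between policies. Power against drug ratios of the same size is below 80% as soon as any patients take the other arm's drug, and the listed inputs make no allowance for this.

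The amount cannot be fixed from the article. Under an assumed loss of 5% to 30% of the contrast, power at a drug ratio of 1.12 is about 76% to 50%, and the detectable drug ratio is about 1.127 to 1.176. At half the event rate, losses of 20% or more take the detectable drug ratio just above the top of the range of 1.1 to 1.2; at one third of the rate, even 5% does (1.201). These results rest on a two-sided alpha of 0.05, on the stated precision being correct, and on d covering only patients who take the other arm's drug. They do not show that the trial is underpowered by a known amount. The point merits correction because the figures are read against plausible drug effects.

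**What to change.** Label 1.12, 1.16 and 1.19 as relative risks between policies (intention-to-treat). Beside each, give the drug ratio detectable with 80% power, exp(ln RR / (1 − d)), for a stated range of d covering only opt-out, switch-back and off-policy prescribing. Base the range on uptake in the trial or in the pilot that began in October 2017, if uptake was recorded; the article reports no such rates.

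Keep complete discontinuation out of d, since it can move the policy ratio in either direction, and explore it as a separate scenario in the simulation.

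The cost is a re-run of the existing simulation and a somewhat less favourable stated figure. Sample size, design and primary analysis are unchanged.

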## Study conduct

### Study management group

An executive study committee will be constituted to guide the day to day running of the study. This group will consist of three of the principal investigators. An external advisor will be invited to join the study executive.

